## Abstract

**Background:**

Despite high acceptance rates in the field, the implementation of the 2019 published German evidence and consensus-based S3 guideline is unsatisfactory. This study aims to assess the superiority of an adaptive online version with a better visualization of the recommendations in terms of guideline conformity, application of shared decision making, and digital health expertise compared to the classic pdf print version of the guideline.

**Methods:**

The study is a multicenter, controlled, cluster-randomized trial with two arms: one arm investigating the implementation of the German schizophrenia guideline in form of a digital format (intervention group using the evidence ecosystem MAGICapp), the other arm in form of the classic print pdf version (control group). Physicians and psychologists working in specialized hospitals will be included in the study. The guideline-knowledge before and after the intervention is defined as primary outcome measure. Secondary endpoints include digital health expertise and application of shared decision making.

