### Randomization

The sequence of randomization and the randomization list of the clusters will be performed by a statistician experienced in the method using the Mersenne-Twister algorithm. Randomization is balanced according to the number of clusters (see below) and the structure of the hospitals (university hospitals, large community hospitals, small community hospitals). All statistical analyses will be conducted blindedly as the statistician performing the analyses has no knowledge of which clinic and cluster belong together. A statistical analyses plan will be developed before closing the database.

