### Study design

This study is a multicenter, controlled, cluster-randomized, two-arm trial with both arms investigating the implementation of the German schizophrenia guideline. One arm (intervention) in form of an adaptive digital format and the other arm (control) in form of the classic pdf print version. A cluster randomization was chosen in order to avoid discussions between the participants of one organizational unit and thus contamination, which would have been likely to occur with an individual randomization [24]. The trial has been approved in ethical and legal terms by the local ethics committee of the medical faculty of the LMU, Munich (reference number 21-0780) and the involved data protection officer (reference number 1819.b.).

The study involves 17 clinics for psychiatry and psychotherapy in the regions of Swabia and Upper Bavaria, Germany. As these clinics have more than 13,000 employees and provide care for about three million inhabitants, they are the main supplier for people with schizophrenia in South Bavaria. Those 17 clinics are allocated to 14 clusters (see Table 2). A stakeholder of a TUM-located self-aid group is involved in the SISYPHOS Project.

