### Recruitment procedure and study flow

The recruitment and data collection will be conducted from March 2022 until November 2022. Participants fulfilling the inclusion criteria and having signed informed consent start with the baseline survey (T0). In detail, recruitment and obtaining informed consent was locally performed by the respective hospital directors who were authorized by the responsible ethical board. Signed ICs will be sent to the study coordinator [name]. Participation was only possible upon presentation of the signed consent form. After receiving the signed IC, the leading study center provides the link for the baseline survey. When the link was opened, participants will be again asked to confirm their participation and were informed about all data protection standards. The team of the University of Augsburg ([name]) coordinated the whole process. They advertise for participation in the study via emails and video conferences, sent the links for the survey, and perform the trainings. In more detail, for the baseline assessment an email is sent with a link to the questionnaire and in addition a pseudonymization code as a replacement for their names using a licensed software LimeSurvey version 5.3.4+ of the LMU Munich. First, a sociodemographic questionnaire comprising 12 questions collects information including, e.g., gender, age, school years, and working experience. Second, we enquire the attitude towards the guideline for schizophrenia as well as a living guideline and the knowledge of the German S3 guideline for schizophrenia (see details below). Afterwards, the intervention follows, either in form of the experimental condition (MAGICapp) or in form of the control condition (print/pdf version) depending on the randomization. Six months later, the intervention stops and the participants are asked to fill in the same questionnaire as at the beginning of the survey (T1) (see Fig. 1, Table 1).

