**Fig. 1 Fig1:**
[figure not shown]
Study design

**Table 1 Tab1:** Overview of examinations at different time points

Time point	Screening	T0	Intervention 6M	T1
Allocation clinics	X			
Inclusion/exclusion criteria	X			
Informed consent	X			
Sociodemographic questionnaire		X		
Questionnaire on guideline knowledge of the S3 Guideline Schizophrenia (primary endpoint)		X		X
eHealth literacy scale		X		X
System Usability Scale		X		X
Provider Decision Process Assessment Instrument		X		X
Participatory Decision Making Questionnaire (PEF-FB-Doc)		X		X
Recording of attitudes and use of the respective formats (traditional print format or MAGICapp)		X		X

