### Outcomes

#### Primary outcome

As primary outcome, guideline conformity among health care providers will be assessed by means of a ‘Questionnaire on guideline knowledge of the S3 Guideline Schizophrenia.’ As a subjective notion of guideline compliance does often not depict reality, the primary outcome is based on case studies developed for this purpose. The questionnaire is developed in correspondence to a publication in the field of internal medicine investigating guideline compliance [25]. For this purpose, 46 casuistic, i.e., case vignette oriented multiple choice questions are asked and a quantitative (number of appropriate answers in relation to the guideline) as well as a qualitative aspect (five cardinal questions were identified as being most important by the investigators and were selected from the 46 questions) will be investigated. Thirty out of 46 items including five correctly answered cardinal questions will be operationalized as guideline compliant and will serve as an evaluation of the effectiveness of the implementation strategies. If less than five cardinal questions were answered correctly, the participant fails, regardless of the number of correct answers. This additionally serves the evaluation of the efficacy of guideline implementation. Differences within the descriptions of the case studies and different sequence of the questions are used for the time points T0 and T1 in order to avoid learning effects.

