### Planned data analysis strategy

For the actual survey, descriptive statistics will be calculated for each center as well as center-overlapping. Descriptive data of drop-outs and completers will be compared. For the primary outcome, a confirmatory hypothesis test will be performed with a two-sided significance level set to 5%. The analysis (Fisher’s exact test) will be based on an intention-to-treat population, which means that all clusters/participants are analyzed as randomized. Drop-out will conservatively be defined as non-compliant guideline adherence. However, we assume a minimal drop-out rate of ≤ 10%, as we examine care providers in two defined service regions. For secondary outcomes with continuous variables, linear mixed model will be applied with inclusion of data with missing values. If normal distribution assumption is violated, monotonous and continuous data transformation (logarithmic or inverse normal transformed (RIN, e.g., rankit)) or non-parametric tests (Mann-Whitney *U* test, Wilcoxon test)) will be used. The per-protocol population will be analyzed in a second step and will be defined as all participants with available T0 and T1 data for the primary outcome measure.

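### The primary Fisher's exact test leaves the T0 result and the hospital-type balancing factor unused: still a valid comparison on that account, but at a modest, assumption-dependent cost in precision

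*Protocol article*

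**What the plan says.** Four parts of the protocol article bear on this point.

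- **Measurement.** The recruitment section and Table 1 place the guideline-knowledge questionnaire, marked as the primary endpoint, at T0 and again at T1 six months later. The abstract (Methods) says: "The guideline-knowledge before and after the intervention is defined as primary outcome measure".
- **Endpoint.** The primary outcome section reduces the questionnaire to pass or fail: "Thirty out of 46 items including five correctly answered cardinal questions will be operationalized as guideline compliant". Anyone who misses a cardinal question fails whatever their total.
- **Randomisation.** "Randomization is balanced according to the number of clusters (see below) and the structure of the hospitals", with three levels: university, large community and small community.
- **Analysis.** "The analysis (Fisher’s exact test) will be based on an intention-to-treat population", with drop-outs counted as non-compliant. Mixed models are named only for continuous secondary outcomes. The article does not say in so many words that the test compares T1 status, but the drop-out rule and the sample size section imply it.

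**The concern.** A 2x2 Fisher test has two inputs, arm and pass/fail status. It has no place for the T0 result or for hospital type, although the first is collected on the same instrument before the intervention starts and the second is known for every cluster.

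Two things are lost. If T0 and T1 results are correlated, part of the T1 variance is predictable and could be removed. And if the arms happen to differ in knowledge at T0, the estimate carries part of that difference, in favour of MAGICapp or against it.

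This is a method the article fixes, not a detail it leaves open. An analysis plan is promised before the database is closed, but one that follows the article cannot add covariates to Fisher's test.

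**Working it through.** **Inputs from the article:** p1 = 0.4, p2 = 0.6, two-sided alpha 0.05, power 0.80, 1:1 allocation, average cluster size 17, ICC 0.01, 14 clusters. **Assumed:** 7 clusters per arm (inferred from balanced randomisation, not stated), equal cluster sizes, a T0 pass rate of 40%, and the T0-T1 correlation, which the article does not give.

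**1. The plan's own figure.** Full enumeration of the two-sided Fisher test at 0.4 versus 0.6 gives power 0.8008 with 102 per arm and 0.7939 with 101, so 204 is reproduced. The design effect is 1 + 16 × 0.01 = 1.16, and 204 × 1.16 = 236.6, or 237. The sample size arithmetic is not at fault here.

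**2. Chance imbalance at T0.** Each arm has 7 × 17 = 119 participants.

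SD of the T0 difference = sqrt(0.4 × 0.6 × (1 + 16 × ICC) × 2/119)

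| ICC | SD (percentage points) | Chance of a gap of 10 points or more |
|---|---|---|
| 0.01 (protocol) | 6.8 | 14% |
| 0.05 | 8.5 | 24% |
| 0.10 | 10.2 | 33% |

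With ICC = 0 the same formula gives sqrt(0.24 × 2/119) = 0.0635, or 6.4 points. At the protocol's ICC, clustering therefore adds only about 0.5 points; the rest is ordinary sampling error.

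**3. How much carries over.** With equal variances at T0 and T1, the expected carry-over is the correlation times the gap. A 10-point gap shifts T1 by about 1, 3 or 5 points at a pass/fail correlation (phi) of 0.1, 0.3 or 0.5, against a planned effect of 20 points.

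**4. Precision recovered for the pass/fail endpoint.** The variance factor is 1 − phi².

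| phi | Variance factor | N equivalent to 237 |
|---|---|---|
| 0.1 | 0.99 | 235 |
| 0.2 | 0.96 | 228 |
| 0.3 | 0.91 | 216 |
| 0.4 | 0.84 | 200 |
| 0.5 | 0.75 | 178 |

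**5. Simulated power.** The simulation used 14 clusters of 17, 4,000 runs per setting, an observed ICC of about 0.01, rates of 0.4 and 0.6, and the same cluster effect at T0 and T1. The correlation here is on the latent scale before the pass/fail cut. Hospital type and drop-out were not modelled.

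| Latent T0-T1 correlation | Cluster-mean t-test, unadjusted | Same test, adjusted for T0 status |
|---|---|---|
| 0 | 0.76 | 0.76 |
| 0.3 | 0.76 | 0.79 |
| 0.5 | 0.76 | 0.84 |
| 0.7 | 0.75 | 0.88 |

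Type I error of both tests lay between 0.047 and 0.052. Fisher's test, which ignores clustering, had power of about 0.81 to 0.82 in the same settings. The gain from T0 is thus a gain over an unadjusted cluster-aware test. It passes the nominal power of Fisher's test at latent correlations of 0.5 and 0.7, but not at 0.3.

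**The case against.** The strongest reply is that an unadjusted comparison of randomised groups is legitimate, because chance baseline differences are part of the sampling error the test allows for. **That stands.** A reader might infer that the test is invalid for want of adjustment; nothing in the article supports this. The same test also ignores clustering, which is a separate and more serious fault. This point neither depends on it nor should borrow its weight.

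Other tempting readings also go too far:

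- **That 14 clusters make large baseline gaps likely.** At the protocol's ICC nearly all the chance imbalance would arise without clustering. The larger figures need ICCs 5 to 10 times the planning value.
- **That university and community hospitals will be unbalanced.** Randomisation is balanced on that factor, so baseline knowledge is the main exposure.
- **That adjustment is worth a third more participants, or that 61 per arm would do.** The first figure takes a correlation of 0.5 on the continuous score (1/0.75 = 1.33). The second takes 0.4 versus 0.6 as one cut on a normal score (d = 0.507; 2 × 2.8²/0.507² = 61). The cardinal-question rule breaks that link to the 0-46 score, so neither figure is a gain for the primary endpoint.
- **That the number correct was announced as an endpoint and then left untested.** The article speaks of "a quantitative (number of appropriate answers in relation to the guideline) as well as a qualitative aspect", but the number correct enters the primary endpoint through the 30-item threshold.
- **That the abstract commits the trial to a change-from-baseline endpoint.** Its wording can be read as saying only when knowledge is measured; the primary outcome and sample size sections define reaching a cut-off.

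It is also fair to say that the T0-T1 correlation may be weak. Case descriptions and question order differ between time points, both arms receive six months of training, and drop-outs are scored as failures. The gain could then be close to nil. Supportive analyses can be left to the analysis plan. The primary test cannot, because the article already names it.

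**Conclusion.** The point holds as a question of efficiency and robustness, not of validity. The article fixes a primary test that cannot use a baseline measurement of its own endpoint or its own balancing factor.

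For pass/fail status the variance saved runs from about 1% to 25% for phi of 0.1 to 0.5. Cluster-level power rises from about 0.76 to between 0.79 and 0.88 for latent correlations of 0.3 to 0.7. A T0 gap of at least half the planned effect has about a 14% chance at the planning ICC, and only part of it would reach the T1 comparison.

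These figures rest on the inferred 7 v 7 split, equal clusters of 17, a 40% T0 pass rate and assumed correlations. The change is worth making because the data are already planned and a cluster-aware primary analysis is needed anyway. The abstract's wording and the absence of a separate score analysis are minor.

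**What to change.** In the planned data analysis section, replace Fisher's test with a cluster-aware comparison of T1 compliance between arms that:

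- applies a small-sample correction suited to 14 clusters;
- adjusts for T0 (score or pass/fail status, chosen in advance) and hospital type;
- reports a prespecified marginal risk difference with its confidence interval.

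One workable form is a two-stage analysis: adjust individual results for the covariates, average the residuals by cluster, and compare the cluster means with a t-test. Code hospital type exactly as in the randomisation list. Table 2 marks only university and community and gives two clusters both marks, whereas the randomisation section has three levels.

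Align the abstract by stating that the outcome is T1 compliance, with T0 as a covariate. The T1 score on the 0-46 scale, adjusted for T0 in the same framework, may be named as supportive.

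**Cost.** No new data are needed, but the named confirmatory test changes, so the article's method must be amended and not merely detailed in the analysis plan. This should be done before the database is closed. Hospital type uses up to 2 of the 12 cluster degrees of freedom (14 − 2 = 12, leaving 10), and the primary model becomes slightly more complex. The analysis file must carry coded cluster and hospital-type labels and a T0-T1 link. The per-protocol definition already presupposes that link, but the data management section says the data table will not record where a survey was completed, so the coding should be made explicit.

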**Discussion:**

This is the first study evaluating if an adaptive-digital version of the schizophrenia guideline is superior to the classic pdf print version. Therefore, the guideline is digitally prepared in the evidence-ecosystem MAGICapp, which covers the whole process of the development of a living guideline. We intend to use the results of the cluster-randomized trial for developing the German S3 guideline for schizophrenia in form of a living guideline in future.

**Trial registration:**

The study is registered (10 May 2022) in the German Clinical Trials Register (DRKS) and the WHO International Clinical Trials Registry Platform (ICTRP) under registration number DRKS00028895.

**Supplementary Information:**

The online version contains supplementary material available at 10.1186/s13063-022-06749-0.

## Background

Guidelines are nowadays a standard of evidence-based medicine [1–3]. However, the implementation in clinical practice remains in many cases insufficient [4–7]. While the development of clinical practice guidelines has been standardized and improved over the last years, the implementation to improve clinical practice remains challenging [8, 9].

In 2019, the German evidence and consensus-based S3 guideline for schizophrenia was published. A recent study has shown that in spite of a high acceptance of this guideline, more than half of the participants did not use the guideline in everyday clinical practice [10]. In that regard, the question arises of identifying and understanding the reasons for this gap between acceptance and implementation.

Possible reasons for poor guideline adherence include several existing barriers (e.g., too long versions, inappropriate form of publication, lack of familiarity concerning the use of guidelines) and not yet comprehensively considered facilitators (e.g., workshops for practitioners about the content of the guideline) [10–12]. Several frameworks aiming to explain insufficient guideline adherence and to categorize the barriers and facilitators of guideline implementation are available [13, 14]. Moreover, guidelines are often already out of date when published due to the exponentially increasing medical knowledge [15, 16]. One potential solution of this problem is the development of so-called living guidelines. In brief, living guidelines optimize the guideline development process by updating individual recommendations as soon as relevant new evidence becomes available or at least once a year [17, 18]. To ensure such a continuous updating of guidelines, digital, internet and platform-independent based concepts of guideline development are required. One such system is the evidence ecosystem called MAGICapp [19], which covers the whole process of developing living guidelines and includes the possibility of publishing “conventional” guidelines. MAGICapp was chosen as according to the ‘Guidelines International Network Tech-Working Group’ this system seems to be superior to other platforms in terms of functionality [20]. Moreover, the Working Group of the Scientific Medical Societies (AWMF) in Germany plans to use this evidence ecosystem in the future [21]. Further important advantages of MAGICapp (e.g., compared to GRADEpro) are the graphical depiction of the evidence in order to support shared decision-making and the interactive potential of the platform due to the comment function allowing users of the MAGICapp browser-based software to give feedback to each recommendation.

A living guideline for schizophrenia in Germany is currently under development and this study aims to examine whether such an optimized online version improves guideline implementation compared to classic implementation strategies.

This cluster-RCT will be the first study to evaluate the effect of a guideline implementation using the evidence-ecosystem MAGICapp within a circumscribed model region in South Germany involving all major hospitals that are involved in the care of people with schizophrenia. Here, we present the concept, design and protocol of this study.

## Methods/design

### Study objectives

This study is part of a project called ‘*Structured implementation of digital, systematically updated guideline recommendations for enhanced adherence in schizophrenia’* (‘SISYPHOS’) [22]. The major part of the project investigates in form of a cluster-randomized controlled trial if an online version with a visualization of the recommendations is superior in terms of guideline conformity, application of shared decision making, and digital health expertise than the classic pdf print version. Therefore, the current German schizophrenia guideline is digitally prepared in the evidence ecosystem MAGICapp [19]. The following protocol presents the design of the cluster-randomized controlled trial. The protocol was prepared in accordance with the SPIRIT reporting guidelines [23] (see Additional file 1).

### Randomization

The sequence of randomization and the randomization list of the clusters will be performed by a statistician experienced in the method using the Mersenne-Twister algorithm. Randomization is balanced according to the number of clusters (see below) and the structure of the hospitals (university hospitals, large community hospitals, small community hospitals). All statistical analyses will be conducted blindedly as the statistician performing the analyses has no knowledge of which clinic and cluster belong together. A statistical analyses plan will be developed before closing the database.

### Study design

This study is a multicenter, controlled, cluster-randomized, two-arm trial with both arms investigating the implementation of the German schizophrenia guideline. One arm (intervention) in form of an adaptive digital format and the other arm (control) in form of the classic pdf print version. A cluster randomization was chosen in order to avoid discussions between the participants of one organizational unit and thus contamination, which would have been likely to occur with an individual randomization [24]. The trial has been approved in ethical and legal terms by the local ethics committee of the medical faculty of the LMU, Munich (reference number 21-0780) and the involved data protection officer (reference number 1819.b.).

The study involves 17 clinics for psychiatry and psychotherapy in the regions of Swabia and Upper Bavaria, Germany. As these clinics have more than 13,000 employees and provide care for about three million inhabitants, they are the main supplier for people with schizophrenia in South Bavaria. Those 17 clinics are allocated to 14 clusters (see Table 2). A stakeholder of a TUM-located self-aid group is involved in the SISYPHOS Project.

